#### Primary outcome measure

Roland Disability Questionnaire for Sciatica (RDQ). This illness-specific 23 item functional assessment questionnaire is frequently used for low back pain and sciatica [19-22]. Scores range from 0 to 23, reflecting a simple unweighted sum of items endorsed by the respondent. Patients with high scores at baseline have a severe disabling sciatica. To define recovery, a difference of at least 11 points from baseline has to be seen. This self report measure of physical disability due to back and leg pain has established validity, reliability, and responsiveness to change [23].

#### Secondary outcome measures

##### 1) Perceived recovery

This is a 7-point Likert scale measuring the perceived recovery, varying from 'complete recovery' to 'worse than ever'. This outcome scale has been used in previous studies and is regarded valid and responsive to change [24]. Next to this global selfassessment, a job and hobby specific Likert will be scored. During the intake of the study the patient will be asked to rank their 5 most important functional disabilities in daily life, which they can use in their own evaluation overall and in separate items.

##### 2) Visual Anolog Scale (VAS) of leg pain

This parameter will measure the experienced pain intensity in the leg during the week before visiting the research nurse. Pain will be assessed on a horizontal 100 mm scale varying from 0 mm, 'no pain', to 100 mm, 'the worst pain imaginable'. Patients do not see the results of earlier assessments and will score the pain experienced at the visit. Reliability, validity and responsiveness of VAS have been shown [25].

##### 3) VAS of back pain and combined leg and back pain

Since many patients with sciatica have back pain as well, we will also measure the intensity of solitary back pain and the combination of leg and back pain. There may be a difference in back pain between the muscle-splitting microendoscopic technique and the conventional muscle-discecting technique.

##### 4) McGill pain questionnaire

Several qualities of perceived pain will be measured using the Dutch version of the McGill Questionnaire [26].

##### 5) Short-form 36 (SF 36)

This is a generic health status questionnaire which can easily be filled out at home. The questionnaire consists of 36 items on physical and social status of the patient subdivided in 8 domains; 1) physical functioning, 2) physical restrictions, 3) emotional restrictions, 4) social functioning, 5) somatic pain, 6) general mental health, 7) vitality and 8) general health perception. The questions are scored on a scale of 0 (worst health) to 100 (ideal health). This questionnaire has been used frequently and is validated in surgical studies on low back pathology [27-29].

##### 6) Sciatica Frequency and Bothersome Index (SFBI)

This is a scale ranging from 0 to 6, which can assess the frequency (0 = never to 6 = always) and bothersome (0 = not at all to 6 = extreme bothersome) of back and leg pain. The sum of the results of four symptom questions yields both indexes, ranging from 0 to 24. The four questions are: leg pain, numbness and/or tingling in leg, weakness in leg or foot, and pain in back or leg while sitting [19,30].

##### 7) Prolo scale

This scale measures the evaluation of the surgeon and research nurse of the patient's functional and economic status. It has been used in outcome studies of lumbar spinal operations [31].

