## Methods/Design

We designed an observer and patient blinded randomised cost-effectiveness trial in the treatment of lumbar disc herniation in which two surgical techniques are compared in a parallel group design. The primary outcome measure is the Roland Disability Questionnaire for Sciatica. The follow-up period will last 2 years. In order to collect enough patients, a multi-center design is necessary. The study protocol was approved in all participating hospitals.

Our primary question is whether MED is more (cost)-effective than open discectomy. The analysis will be focused on the proportion of patients who are recovered to a normal functional situation at the short and long term. Moreover, we want to identify certain subgroups who may benefit more of one of the allocated treatments.

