### Randomisation procedure

Patients will be randomly allocated to either MED or conventional discectomy. Randomisation will take place on the operating room within 4 weeks after the first visit to the research nurse. A randomisation list is prepared for every participating hospital-nurse combination. Variable-sized blocks of random numbers are formed to ensure equal distribution of the randomisation treatments over hospitals and research nurses. The data manager at the department of Biostatistics, who is not involved in the selection and allocation of patients, will prepare coded, sealed envelopes containing the treatment allocation. In the operating room, after induction of anesthesia, the surgeon will open the envelope and the allocated treatment is performed. Patients and research nurses are kept blinded for the allocated treatment during the follow-up period of 2 years.

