### Intervention

Patients will be randomised into conventional unilateral transflaval discectomy (A) or MED (B). Depending on the surgeon and patient's preference, surgery will be performed under general or spinal anesthesia. The patients will be positioned prone and the affected disc level is verified with fluoroscopy. The participating surgeons have large experience in both techniques. A standardized Case Record Form (CRF) will register the surgeon's findings and this CRF, together with the randomisation envelope, will be returned to the data center in a sealed envelope.

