### Outcome assessment

We will use the below described validated outcome parameters which will be assessed by means of questionnaires. Follow-up examinations by the research nurse will take place 4, 8, 26 and 52 weeks after randomisation. Patients will be neurologically examined and questionnaires will be filled in (table 2). In between at 1, 2, 6, 12, 38, 78 and after 104 weeks the main questionnaire (primary outcome measures) will be filled in at home and send to the data center. The outpatient control by the neurosurgeon will be at 8 weeks and more if necessary.

We hypothesise a difference in (cost)-effectiveness between MED and conventional discectomy in favor of the MED on the short term, and comparable (cost)-effectiveness after 6–12 months. Therefore the main questionnaire will be answered at 8 weeks and 1 year after surgery.

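### The observer-blind label does not cover the surgeon's Prolo rating, so the group comparison should use the research nurse's rating only

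*Protocol article*

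**What the plan says.** The Methods/Design section opens with the claim: "We designed an observer and patient blinded randomised cost-effectiveness trial". The Randomisation procedure section names those who are blinded: "Patients and research nurses are kept blinded for the allocated treatment during the follow-up period of 2 years". The surgeon is not among them. The same section says how the allocation becomes known: "In the operating room, after induction of anesthesia, the surgeon will open the envelope and the allocated treatment is performed".

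Under Secondary outcome measures, item 7 (Prolo scale), on the patient's functional and economic status, reads: "This scale measures the evaluation of the surgeon and research nurse". It does not say whether the two ratings are given separately or jointly, or which one is compared between groups. The Statistical analysis section plans between-group differences with 95% confidence intervals for the outcome measures and makes no exception for this scale.

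Two further statements bear on patient blinding. On follow-up, the Outcome assessment section says: "The outpatient control by the neurosurgeon will be at 8 weeks and more if necessary". On anaesthesia, the Intervention section says that, depending on preference, "surgery will be performed under general or spinal anesthesia".

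**The concern.** An outcome rated by someone who knows the treatment can drift towards what that person expects or hopes for. A judgement of functional and economic status leaves room for this. The article records the surgeon's treatment preference and expected recovery at 8 weeks (Baseline data), so these surgeons may hold views about the two techniques.

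If the surgeon's Prolo rating enters the treatment comparison, a difference between groups could reflect the rater as well as the treatment. Someone reading the results under an observer-blind label would have no warning of this. What is at stake is the credibility of one secondary outcome and the accuracy of the design label. The primary outcome, the RDQ, is completed by the patient and is not rated by the surgeon.

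**Working it through.** The article gives no figure for this point and none is needed. The check sets the statements on knowledge of allocation beside those on who assesses outcomes.

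1. **Who knows the allocation.** The surgeon opens the envelope and performs the assigned operation (Randomisation procedure). Blinding the operator is impossible here, and the article does not claim it.

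2. **Who is stated to be unaware.** Patients and research nurses for 2 years (Randomisation procedure), and the physician who discharges the patient (section on microendoscopic discectomy).

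3. **Who rates the Prolo scale.** The surgeon and the research nurse. Combining steps 1 to 3:

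| Prolo rater | Knows allocation? | Consistent with observer blinding? |
|---|---|---|
| Research nurse | No, as stated | Yes |
| Surgeon | Yes | No |

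This takes the surgeon in the Prolo item to be the operating surgeon. The article uses the same term in both places and introduces no separate surgeon-assessor.

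4. **Whether the rating reaches a comparison.** Prolo is a listed secondary outcome, and group differences are planned for outcome measures. Nothing keeps the surgeon's rating out. Followed as written, an unblinded rating can enter the treatment comparison.

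5. **Whether the same reasoning reaches the primary outcome.** It does not. The RDQ is a self-report, so the surgeon's knowledge could matter only if it reached the patient. Two routes are conceivable:
   - *The 8-week control.* It coincides with one of the two primary time points, and the article does not place it before or after the questionnaire. It also does not say that the neurosurgeon seen is the one who operated, or that the allocation is discussed.
   - *Spinal anaesthesia.* The envelope is opened after induction, whichever type is used. Spinal induction does not by itself imply unconsciousness, so this timing alone does not conceal the allocation from every patient. The article does not say whether such patients are awake, sedated or able to hear the allocation.

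   Each is a possible route. Neither is a contradiction in the text.

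6. **Size.** A bias estimate would need the effect of knowing the allocation on the surgeon's scoring. For the RDQ it would need the share of patients unmasked in each arm and the effect on their answers. The article gives none of these, so no size is calculated.

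**The case against.** The best defence is that the article makes clear whom it means by observer. Each time it names the blinded parties, including in the Discussion, it lists patients and research nurses. On that reading the label is a claim about the nurse and is true. The Prolo scale is the last of seven secondary outcomes and has a blinded rating available. The choice of rating to analyse is often left to an analysis plan, and the follow-up table that might say more is not shown.

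Much of this stands, and it limits the point to the surgeon's rating. It does not remove the point. On the defence's own reading, an outcome in a trial labelled observer blinded is still rated by someone outside the blind. The article does not mark that rating as different.

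A reader might go further and infer that patient blinding is broken, and that the primary 8-week comparison is therefore biased, because patients meet a neurosurgeon at that time and some may be awake in theatre. The documents do not support this. The gaps on visit order and on concealment in theatre are operational details that a journal article commonly leaves to the full protocol. The article also states real safeguards: incisions of equal length, return of the case record form and envelope under seal, a discharging physician who is unaware of the treatment, and a commitment to keep patients blinded for 2 years. Nor does the recording of patient preference show a direction of bias. The scale runs symmetrically from one technique to the other, and the article gives no reason for collecting it.

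**Conclusion.** The point holds for the surgeon's Prolo rating. The surgeon knows the allocation and is a named rater of a secondary outcome, so that rating is not observer blinded and is open to assessor bias. The conclusion assumes only that the surgeon who rates is the surgeon who operated, which is the natural reading. It does not depend on material outside the article.

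The extent is limited: one of two ratings, on one secondary outcome, with a blinded rating already collected. The size of the bias is unknown and cannot be obtained from the document.

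For patient blinding, and so for the RDQ, the article shows two possible risks and no breach. An inflated type I error for the primary comparison should not be claimed, because any such figure would rest wholly on assumed rates and effects of unmasking.

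**What to change.** **Prolo scale.** State that the between-group comparison uses only the research nurse's rating, made independently of the surgeon's. Report the surgeon's rating by group, labelled unblinded and descriptive. In the design description, say that observer blinding refers to the research nurse. No new data are needed, since the nurse already rates the scale. The small cost is that the surgeon's judgement no longer counts in the treatment comparison.

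**8-week RDQ.** As a precaution, require the 8-week questionnaire to be completed before the neurosurgeon's 8-week control. A research nurse visit already falls in that week, so this takes one sentence and some attention to scheduling. It would not cover extra neurosurgical contacts before 8 weeks, which the article allows when necessary.

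Neither change alters treatment or the choice of anaesthesia, and neither needs extra staff or visits. If the full protocol already contains these provisions, a cross-reference is enough.

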#### Other outcome measures

##### 1) Costs

The direct medical costs of hospital admission and surgery will be based on an integral cost-analysis in three regional participating hospitals. From this institutional analysis, the constant costs per admission and the variabel costs per admission day will be estimated. Knowing the duration of hospitalisation, the individual costs of all operated patients can be estimated. Other medical costs (including physiotherapy, visits to general practioners and medical specialists, nursing care and medication) will be registered in a diary. In the diary the patient will also register non-medical costs (including time costs, travel expenses and domestic help). The research nurse will go through the diary with the patient on every follow-up moment throughout the study period of 2 years. To estimate the indirect costs, like productivity costs, patients will register absenteeism in the diary and the research nurse will register the patient's work situation, work efficiency and gross income on follow-up moments. Absenteeism will be valued to the friction-cost method.

##### 2) Incidence of re-operations

In general, re-operation is considered as bad outcome and therefore used as an outcome measure. The incidence of re-operation in both groups will be measured.

##### 3) Complications

A systematic assessment of complications (including wound infection, deep venous thrombosis, urine tract infection, hematoma, and progressive neurological deficit) will be carried out by the surgeon and research nurse. Moreover, surgeons will be asked for perioperative complications like cerebrospinal fluid leakage, nerve root damage, and exploration on the wrong disc level.

##### 4) Serum creatine kinase (CK)

Creatine kinase is a known marker of muscle damage. The post-operative serum level of CK has a maximal value on day 1 after spinal surgery [17]. Therefore, we will determine the serum CK before surgery and 1 day after surgery in both groups to assess a possible correlation between CK and extent of surgery, i.e. transmuscular versus muscle discection. Whether CK is correlated with back pain and recovery will also be determined.

### Sample size

The sample size is calculated on the basis of the Roland Disability Questionnaire for Sciatica. A difference in effect between MED and open discectomy is assumed whenever MED will obtain at least 20% difference in Roland score at 8 weeks after randomisation. Conventional open discectomy is assumed to have at least 60% good result 8 weeks after surgery. This means that MED is proven to be more effective than conventional surgery whenever 80% or more of the patients have a good outcome 8 weeks after surgery. The numbers used for this sample size are drawn from the Maine Lumbar Spine Study 1 year and 5 year results and were discussed in detail recently [19,21].

This trial attempts to enroll 300 patients with lumbar disc herniations (150 patients in both treatment groups, including 8% loss to follow-up) which is regarded sufficient to detect a difference of 20% (α = 0,05 and a power of 90%) in the primary outcome.

### Statistical analysis

Baseline comparability will be analysed by descriptive statistics to determine whether randomisation was successful. Whenever necessarry, adjustments for baseline variables will be performed in the analysis. Differences in outcome measures between both groups, together with 95% confidence intervals, will be calculated. Besides a difference in recovery between the two groups, analysis of a difference in time to recovery will be carried out as well. All data are analysed according the "intent-to-treat principle". In addition, an explorative subgroup analysis is conducted to investigate whether the treatment effect varies over specific subgroups of patients (table 3). Data will be stored via the internet-based secure data management system "ProMISe" of the department of Medical Statistics and Bioinformatics. The analyses will be carried out using appropriate statistical software (e.g. SPSS).

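### Baseline adjustment is triggered by observed imbalance instead of being fixed in advance, which gives up precision from baseline RDQ and leaves the primary estimate open

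*Protocol article*

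**What the plan says.** The Statistical analysis section opens with "Baseline comparability will be analysed by descriptive statistics to determine whether randomisation was successful" and continues "Whenever necessarry, adjustments for baseline variables will be performed in the analysis". Read in order, the second sentence acts on what the first one finds. The section then promises between-group differences with 95% confidence intervals. It names no covariate, gives no criterion for necessity, and does not say whether an adjusted or an unadjusted estimate is primary.

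Three other places bear on this:

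- Primary outcome measure: the RDQ runs from 0 to 23, and recovery requires a change of at least 11 points from baseline.
- Patients: the questionnaires and outcome measures are recorded after consent, before surgery, so every patient should have a baseline RDQ.
- Randomisation procedure: "A randomisation list is prepared for every participating hospital-nurse combination", and "Variable-sized blocks of random numbers are formed to ensure equal distribution of the randomisation treatments over hospitals and research nurses". The Statistical analysis section neither includes nor excludes these factors.

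**The concern.** Allocation comes from lists and sealed envelopes prepared by a data manager who takes no part in selecting or allocating patients. If that procedure is followed, baseline differences between arms are chance. They do not show whether randomisation worked, and their size does not show which covariates are worth adjusting for. A covariate earns its place through its relation to outcome, and that can be judged before any data are seen.

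Baseline RDQ is a clear case. A patient who starts below 11 cannot improve by 11 points, so the baseline score bears on the recovery endpoint by arithmetic alone. Making its use depend on observed imbalance has two consequences:

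- In most trials no imbalance would look notable, so the default is an unadjusted comparison that leaves available precision unused.
- With no criterion and no named primary estimate, an analyst could defend either result after seeing both.

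**Working it through.** **Inputs from the article (Sample size section).** "α = 0,05 and a power of 90"%; "Conventional open discectomy is assumed to have at least 60% good result 8 weeks after surgery"; for MED, "80% or more of the patients have a good outcome 8 weeks after surgery"; and "150 patients in both treatment groups, including 8% loss to follow-up". Evaluable patients per arm: 150 × 0.92 = 138.

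**Assumptions, because the article gives no figures.** The test is two-sided. A good result is a yes/no outcome whose correlation r with baseline RDQ is 0.3 to 0.5. The number of hospital-nurse strata is 6 or 10, and the between-stratum SD is 0 to 1.0 on the logit scale.

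**1. The plan's own sample size.** Per arm, n = [1.96√(2 × 0.7 × 0.3) + 1.2816√(0.6 × 0.4 + 0.8 × 0.2)]² / 0.2² = (1.270 + 0.811)² / 0.04 ≈ 108.2, so 109. After 8% loss, 109 / 0.92 = 118.5, so 119 per arm and 238 in total. With a continuity correction it is 119, then 130 per arm, 260 in total. The stated 300 is not reproduced; it is larger than its inputs need. That is a separate matter, but it explains why the power at stake below is small.

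**2. Unadjusted power at 138 per arm.** z = [0.2√138 − 1.96√0.42] / √0.40 = (2.350 − 1.270) / 0.632 = 1.71, giving power of about 95.6%.

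**3. Gain from planned adjustment.** Residual variance is multiplied by 1 − r², and interval width by √(1 − r²). Putting the effective number per arm, 138 / (1 − r²), into the formula of step 2:

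| r | Variance cut | Interval narrower by | Effective n per arm | Power |
|---|---|---|---|---|
| 0.3 | 9% | 1 − √0.91 = 4.6% | 151.6 | 97.0% |
| 0.5 | 25% | 1 − √0.75 = 13.4% | 184 | 98.9% |

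A simulation of the binary outcome with linear adjustment for one covariate gave the same figures: 97.0% and 98.9%, against 95.9–96.0% unadjusted.

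**4. What a conditional rule recovers.** Simulation: 138 per arm, continuous outcome, effect 0.39 SD (chosen so that unadjusted power is about 90%), 1 or 5 covariates. Imbalance significant at 5% stands in for the undefined criterion.

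| Analysis | Power | Type I error |
|---|---|---|
| Unadjusted | about 90% | 4.9–5.4% |
| Adjust only for imbalanced covariates | 90–91% | 4.3–5.3% |
| Planned adjustment, r = 0.3 | about 92% | 5.1–5.7% |
| Planned adjustment, r = 0.5 | about 96% | 5.1–5.2% |
| Better of adjusted and unadjusted | not a valid comparison | 6.6–7.5% |

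Each type I figure rests on 8,000 replicates, so its standard error is about √(0.05 × 0.95 / 8000) = 0.24 points. The conditional rule recovers little because a single covariate crosses a 5% threshold in only about 1 trial in 20.

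**5. Strata.** Pooled test against the Cochran-Mantel-Haenszel test, 60% versus 80%. The arms are 138 with 6 strata and 130 with 10, because strata were kept equal in size.

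| Stratum SD (logit) | Power gain from stratifying | Type I error of pooled test |
|---|---|---|
| up to 0.5 | at most 0.4 points | 4.4–4.7% at SD 0.5 |
| 0.8 | 0.8–0.9 points | 3.8–3.9% |
| 1.0 | 1.2–1.3 points | 3.2–3.3% |

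**The case against.** The best defence is that this is a condensed article, and that covariates and the primary model normally belong in an analysis plan that is not shown. That holds for detail the article leaves out. It does not cover the adjustment rule, which the article states, and which would be a poor rule in any plan that carried it forward.

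Three stronger readings are tempting, and the document supports none of them:

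- *The strata are left out of the analysis.* The Statistical analysis section is silent on them. Model terms for stratification factors are commonly left to the fuller plan. The one hint of hospital differences, admission of 2–7 days by usual care, concerns length of stay and not RDQ. Even if the strata were ignored, the loss is small and the test errs on the conservative side.
- *The rule inflates type I error.* The 6.6–7.5% arises only if both analyses are run and the better one is reported, which the article does not propose. A mechanical imbalance rule did not inflate the error. The article also speaks of descriptive statistics, so the significance trigger simulated here is a stand-in for its procedure.
- *The trial loses much power.* Larger losses appear at smaller effects: at 0.3 SD, power is about 70% unadjusted and 74–82% with planned adjustment. The article states no such effect. At its own 60% versus 80% the loss is about 1 to 3 points.

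**Conclusion.** The point holds as a low-cost improvement to a stated rule; it does not threaten the trial's validity. Tying adjustment to observed baseline comparability is unsound in principle and forgoes most of the precision that baseline RDQ could supply. The gain from planned adjustment is intervals about 5–13% narrower and, at the stated design effect, power of about 97–99% instead of about 96%. These sizes depend on the assumed correlation of 0.3–0.5 and shrink if it is lower: at r = 0.2 simulated power is 96.5%. The room to choose between results is real, because no primary estimate is named, but it is a risk and not something the plan prescribes. The strata are secondary: it is enough to confirm that the full plan accounts for them.

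**What to change.** Replace the adjustment sentence with:

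> *The primary analysis of the RDQ endpoints adjusts for baseline RDQ and the randomisation stratum (hospital-nurse, or hospital if strata are sparse), whatever the observed balance. For recovery, the covariate-standardised risk difference is reported. Baseline tables are descriptive only, and the unadjusted result is a sensitivity analysis.*

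Drop the statement that the baseline comparison determines whether randomisation succeeded. If a fuller analysis plan exists, check that it says the same.

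The cost is wording only. Baseline RDQ is already collected, and hospital and nurse are known from the randomisation lists. No patients, visits or measurements are added. The change should be made before anyone sees outcome data by arm.
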